# Testing a Model of Care for Patients on Immune Checkpoint Inhibitors Based on Electronic Patient-Reported Outcomes: Protocol for a Randomized Phase II Controlled Trial

**DOI:** 10.2196/48386

**Published:** 2023-10-18

**Keywords:** patient-reported outcomes, model of care, immune-related adverse events, remote symptom management, self-management support, self-efficacy, health-related quality of life, eHealth, telehealth, support, self-management, symptom, monitoring, cancer, electronic health record, immune, detection, questionnaire, treatment

## Abstract

**Background:**

Management of severe symptomatic immune-related adverse events (IrAEs) related to immune checkpoint inhibitors (ICIs) can be facilitated by timely detection. As patients face a heterogeneous set of symptoms outside the clinical setting, remotely monitoring and assessing symptoms by using patient-reported outcomes (PROs) may result in shorter delays between symptom onset and clinician detection.

**Objective:**

We assess the effect of a model of care for remote patient monitoring and symptom management based on PRO data on the time to detection of symptomatic IrAEs from symptom onset. The secondary objectives are to assess its effects on the time between symptomatic IrAE detection and intervention, IrAE grade (severity), health-related quality of life, self-efficacy, and overall survival at 6 months.

**Methods:**

For this study, 198 patients with cancer receiving systemic treatment comprising ICIs exclusively will be recruited from 2 Swiss university hospitals. Patients are randomized (1:1) to a digital model of care (intervention) or usual care (control group). Patients are enrolled for 6 months, and they use an electronic app to complete weekly Functional Assessment of Cancer Therapy-General questionnaire and PROMIS (PROs Measurement Information System) Self-Efficacy to Manage Symptoms questionnaires. The intervention patient group completes a standard set of 37 items in a weekly PROs version of the Common Terminology Criteria for Adverse Events (PRO-CTCAE) questionnaire, and active symptoms are reassessed daily for the first 3 months by using a modified 24-hour recall period. Patients can add items from the full PRO-CTCAE item library to their questionnaire. Nurses call patients in the event of new or worsening symptoms and manage them by using a standardized triage algorithm based on the United Kingdom Oncology Nursing Society 24-hour triage tool. This algorithm provides guidance on deciding if patients should receive in-person care, if monitoring should be increased, or if self-management education should be reinforced.

**Results:**

The Institut Suisse de Recherche Expérimentale sur le Cancer Foundation and Kaiku Health Ltd funded this study. Active recruitment began since November 2021 and is projected to conclude in November 2023. Trial results are expected to be published in the first quarter of 2024 and will be disseminated through publications submitted at international scientific conferences.

**Conclusions:**

This trial is among the first trials to use PRO data to directly influence routine care of patients treated with ICIs and addresses some limitations in previous studies. This trial collects a wider spectrum of self-reported symptom data daily. There are some methodological limitations brought by changes in evolving treatment standards for patients with cancer. This trial's results could entail further academic discussions on the challenges of diagnosing and managing symptoms associated with treatment remotely by providing further insights into the burden symptoms represent to patients and highlight the complexity of care procedures involved in managing symptomatic IrAEs.

**Trial Registration:**

ClinicalTrials.gov NCT05530187; https://www.clinicaltrials.gov/study/NCT05530187

**International Registered Report Identifier (IRRID):**

DERR1-10.2196/48386

## Introduction

Immune checkpoint inhibitors (ICIs) have increasingly become part of the standard treatment for multiple cancer types and stages, with the main benefits including superior overall survival rates [1-14]. Although ICIs are generally considered as well-tolerated, they may trigger immune-related adverse events (IrAEs), which can be severe and result in debilitating or fatal outcomes [15,16]. Treatment modality, cancer type, and patient characteristics appear to influence the likelihood of symptomatic IrAEs, which generally occur in 40%-80% of patients [10,15]. Combinations of ICI agents generally result in a higher incidence and severity of symptoms, with 55% of IrAEs being severe (grade 3 or higher) [15,17]. Even though the incidence of IrAEs appears to be positively correlated with superior objective response rates to ICIs, the occurrence of severe events may lower overall survival rates [2,18]. It is posited that solid tumors that exhibit high mutational burden elicit a stronger immune response, which may trigger more IrAEs [19,20]. Limited evidence suggests that skin, respiratory, renal, and hepatic IrAEs also appear to be correlated with melanoma, lung cancer, kidney cancer, and hepatocellular cancers, respectively, suggesting that different tumor types may increase the likelihood of specific IrAEs [21-23]. In addition, genetic risk factors such as allelic variations of *HLA-B* and mutations in the *TMEM162* gene are correlated with higher or lower likelihood of IrAEs [24]. Recent studies have highlighted that the potential chronicity of IrAEs could further burden patients and contribute to lower overall quality of life [16,25-27]. The timing of detection and intervention of IrAEs appears to play a key role in limiting their progression and outcome [10,15,28].

Although most IrAEs occur within the first 3-6 months of the start of treatment, some may develop after a year even when treatment has been discontinued [15,29,30]. In addition to the uncertainty of when they may manifest, IrAEs are heterogenous in their symptomatic presentation and are usually related to the affected tissue or organ [15]. Therefore, patients need to be ready to engage in self-care activities to self-monitor and self-manage symptoms they confront outside of the clinical environment during the multiple weeks between treatments [31].

As clinicians rely on patient recall to assess symptomatic adverse events, the time between visits and the clinician’s own judgement may inadvertently contribute to an underestimation of their severity, frequency, and burden [32,33]. Collecting patient-reported outcomes (PROs) has become a standard to accurately describe symptomatic adverse events by avoiding some of the biases of clinician reporting, thus contributing evidence on safety, tolerability, and efficacy of cancer treatments [34,35]. Recent studies show that PRO data collected electronically can enable more timely interventions to support patients in managing symptoms, resulting in improvements in overall survival, health-related quality of life (HRQoL), symptom control, and patients’ perceived self-efficacy [34,36,37]. Improvements and smaller declines in HRQoL have been observed when actionable PRO data are available to clinicians [38]. PROs can improve communication between patients and health care professionals by increasing the scope of symptoms addressed and how often they are discussed [34].

Clinical trials using electronic PROs (ePROs) in remote symptom management have noted how these data enable interventions that prevent complications related to cancer treatment, leading to similar or lower rates of hospital admissions and emergency care admissions than the current standard of care [36,37]. These models of care generally interpret ePRO symptom data that nurses use to provide personalized remote symptom management support to patients or that activate automated feedback through custom algorithms [36,37,39]. These interventions have seldom been detailed on the procedures put in place to monitor and manage ePRO symptom data. We thus hypothesized that a structured and standardized ePRO-based model of care, including remote monitoring and symptom management, using real-time data may reduce the time to detection of symptomatic IrAEs. This would, in turn, facilitate timely intervention and limit worsening of patients’ HRQoL and perceived self-efficacy to manage their conditions. This randomized controlled trial (RCT), the IePRO (IrAEs monitoring through electronic PROs) trial, aims to verify the effect of an ePRO-based model of care on the time to detection of symptomatic IrAEs.

## Methods

### Project Context

The RCT described in this protocol is the third phase of the IePRO project, which began in the year 2020. The first phase focused on the development of a PRO measure based on the PRO version of the Common Terminology Criteria for Adverse Events (PRO-CTCAE) [40]. The development of this measure has been detailed in a previously published Delphi study [41]. The second phase was concerned with the development of the ePRO-based model of care being tested in the RCT [42]. This is a 2-arm RCT taking place in the ambulatory care oncology units of 2 university hospitals in French-speaking Switzerland since 2 years. Its overall aim is to compare an ePRO-based model of care that enables remote monitoring and management of symptoms to usual care for patients with cancer receiving ICIs exclusively for up to 6 months.

### Study Population

#### Setting

Patients are being recruited in the Department of Oncology of the 2 university hospitals. They receive treatment and have same-day follow-up appointments at the hospitals’ outpatient clinics. Both sites include tumor type–oriented clinical oncology teams with treatment strategies dictated by multidisciplinary tumor boards.

#### Eligibility Criteria

Participants fulfilling all the following inclusion criteria are eligible for this study: (1) patients 18 years old or older, (2) diagnosed with cancer, (3) starting or restarting systemic single- or dual-agent ICI monotherapy in neoadjuvant, adjuvant, consolidation, or palliative settings, and (4) providing informed consent as documented by the signature on the informed consent form. The presence of any of the following exclusion criteria will lead to participant exclusion: (1) patients self-declaring not being able to use the electronic app and complete the questionnaire in French, (2) patients with any psychological, familial, or sociological condition and linguistic limitation, potentially hampering compliance with the study protocol requirements or follow-up procedures, (3) patients restarting ICI therapy who have previously participated in this study, (4) patients with cognitive impairment, as declared in the patient record, and (5) patients participating in other interventional clinical studies.

#### Screening and Enrollment

Patients are identified by the local principal investigator and a team of sub investigators. Potentially eligible patients are approached after clinician appointments or during treatment. They are given the informed consent form (Multimedia Appendix 1), and a telephone call with a subinvestigator is scheduled within the following week to answer any questions or concerns. Patients are given at least 48 hours to consider participating in the study. Figure 1 shows the flowchart for patient enrollment in this study. Informed consent forms are collected during the patients’ next hospital appointment. Patients can be enrolled in the study up to a week after ICI treatment has started. When eligible patients refuse to participate, their reason for refusal is anonymously recorded with their consent.

**Figure 1 figure1:**
[figure not shown]
Flowchart of the enrollment of the patients in this study. ICI: immune checkpoint inhibitor.

### Study Design

Prior to randomization, subinvestigators collect demographic, medical history, and active treatment data from eligible consenting patients. Participants are randomized by subinvestigators using a web-based REDCap (Research Electronic Data Capture) form (version 12.4.21) [43]. The form has a randomization table (1 per site) using permuted block 1:1 randomization (block size of 4), independently prepared by the study biostatistician. Initially, the IePRO RCT was open to patients with melanoma and patients with lung cancer exclusively, and randomization was stratified by cancer type. Due to challenges in recruitment and following a protocol amendment in April 2022, this study was open to patients with all cancer types, and the stratification criteria were dropped. Blinding was not possible due to the nature of the intervention. Patients are informed that they will be randomly allocated to 1 of the 2 models of care: the standard model (control group) or the digital model (intervention group). The informed consent form and support documentation for the electronic app used to deliver the PRO questionnaires include these same conventions to further mitigate the adverse effects of the lack of blinding toward participants. Data collection instructions and reminders sent to clinicians caring for participants do not indicate which group the participant belongs to.

Patients in both groups obtain access to an electronic mobile app, which contains weekly questionnaires for HRQoL and self-efficacy to manage symptoms. An information sheet detailing how to navigate the app is also provided. Nurses and subinvestigators are available to assist patients in installing the app, registering and signing into an account, and replying to the baseline questionnaires in-person or over the phone. Patients in the intervention group have access to a symptoms questionnaire that is part of the intervention being tested. Automated reminders via emails or push notifications are sent to patients when a new questionnaire is available. Patients in both groups have the same number of scheduled clinician appointments—usually the same day and frequency of the ICI treatment—and are followed up for up to 6 months of ICI treatment.

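### A single fixed block size of 4 per site, in an open-label trial where the recruiting role also randomises, makes up to a third of allocations predictable; vary the blocks if recruitment is still open and check for selection

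*Protocol article*

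**What the plan says.** Under Study Design the article gives one randomisation table per site and describes "permuted block 1:1 randomization (block size of 4), independently prepared by the study biostatistician". On who operates it: "Participants are randomized by subinvestigators using a web-based REDCap" form. On masking: "Blinding was not possible due to the nature of the intervention". The only masking measures described are neutral names for the two arms in patient materials, and reminders to treating clinicians that do not reveal the arm.

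Under Screening and Enrollment, "Patients are identified by the local principal investigator and a team of sub investigators", and "a telephone call with a subinvestigator is scheduled within the following week to answer any questions or concerns". Patients have at least 48 hours to decide, hand in the consent form at their next hospital visit, and may be enrolled up to one week after treatment starts. Study Design places consent and baseline data collection before randomisation.

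Until the April 2022 amendment, randomisation was also stratified by cancer type; that stratification was then dropped. The article does not say that block sizes vary, or that the block size is withheld from the people who recruit. The limitations in the Discussion cover dropped stratification, surveillance bias and unblinded patients, but not the predictability of allocation.

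**The concern.** In an unblinded trial the site staff can know past allocations. With a constant block size those past allocations determine some future ones, however well the list itself is hidden. The role that can see this pattern is also the role that recruits.

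There is some room to act on it. One exclusion criterion rests on judgement: any psychological, familial or sociological condition "potentially hampering compliance with the study protocol requirements or follow-up procedures". The order in which patients are approached can also shift a little.

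The primary outcome is the detection date minus the patient's self-reported onset date, so it depends on how promptly a patient reports. If patients expected to report promptly went more often to one arm, the main comparison would be biased. The covariates planned under Statistical Methods (cancer type, age, treatment regimen) do not measure promptness.

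**Working it through.** **Inputs.** Blocks of 4, 1:1, one table per site, two sites (Study Design). Target of 198 randomised and 138 required before attrition, SD 3.65 days, target difference 2 days (Sample Size Calculation). One-sided hypothesis at 5% (Statistical Methods). The article gives no figure for predictability, so there is none to reproduce.

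**1. Predictability at the moment of randomisation.** There are 6 equally likely balanced sequences in a block of 4.
- Position 1: never certain; best guess right 1/2 of the time.
- Position 2: never certain; best guess 2/3.
- Position 3: certain when the first two match (2 of 6 sequences); best guess 1/3 × 1 + 2/3 × 1/2 = 2/3.
- Position 4: always certain; best guess 1.

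Share certain: (0 + 0 + 1/3 + 1)/4 = 1/3. Best guess: (1/2 + 2/3 + 2/3 + 1)/4 = 17/24 = 70.8%. One third of 198 is 66. With 99 patients per site (an assumed even split) the last block is incomplete: 24 × 4/3 + 1/3 = 32.33 per site, or 64.7 in all (32.7%). Simulation gives the same mean, with a 95% range of 59 to 71.

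**2. Predictability when a patient is approached.** Suppose one other patient in the same list is randomised in between. By the number already allocated in the current block:
- 0 allocated: target is position 2, nothing known; best guess 1/2.
- 1 allocated: target is position 3, one allocation known; best guess 2/3.
- 2 allocated: target is position 4, two known; certain with probability 1/3; best guess 2/3.
- 3 allocated: target opens the next block; best guess 1/2.

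Share certain: (1/3)/4 = 1/12 = 8.3%. Best guess: (1/2 + 2/3 + 2/3 + 1/2)/4 = 7/12 = 58%. With two patients in between, nothing is certain and the best guess is (1/2 + 2/3 + 1/2 + 1/2)/4 = 13/24 = 54%.

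**3. How likely an intervening patient is.** Assuming steady accrual and equal sites, 198/(24 × 2) = 4.1 patients per site per month, or about one a week. Consent takes at least 48 hours and may take a week or more, so both step 1 and step 2 are realistic.

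**4. What varying the blocks would do.** This is a simulation of 99 allocations per site against a guesser who knows the set of sizes but not their order.

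| Block scheme | Certain | Best guess right |
|---|---|---|
| Fixed 4 (complete blocks) | 33% | 71% |
| Random 4, 6 | 6% | 69% |
| Random 2, 4, 6 | 4% | 70% |
| Random 4, 6, 8 | 2% | 68% |

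**5. Illustration of possible bias (assumed, not from the article).** Suppose every certain slot is steered: patients placed in intervention have an expected delay η days shorter than average, and those placed in control η days longer. The arms then differ by 2η times the share steered. The standard error with 69 per arm is 3.65 × √(2/69) = 0.62 day. The type I error is P(Z > 1.645 − bias/0.62).
- One third steered: η = 0.25 gives 0.17 day and about 8%; η = 0.5 gives 0.33 day and about 13%.
- One twelfth steered: η = 0.25 gives 0.04 day and about 6%; η = 0.5 gives 0.08 day and about 7%.

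Full steering is the worst case for each share.

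**The case against.** The strongest reply is that fixed small blocks are common and their weakness is generic. The list is prepared independently and sits behind a web form, consent precedes randomisation, and the one-week limit after treatment start restricts holding a patient back for a preferred slot. Most exclusions are not discretionary: inability to use the app is self-declared, and cognitive impairment comes from the record. Both arms use the app weekly, so expected skill with it is a weak motive for preferring an arm. All of this stands and lowers the risk. None of it stops someone inferring the next allocation from earlier ones.

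The one-third figure describes the moment of randomisation and overstates what is known at approach. That is correct, and step 2 gives the lower figures.

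Three stronger readings are tempting, and the article supports none of them.
- That publication gave the block size away. The article is dated 18 October 2023, and recruitment ran from November 2021 with projected close in November 2023. Publication came about a month before the end and adds little.
- That subinvestigators were told the block size, or that the same individuals recruit and randomise. The article is silent on disclosure, and it names a role and a team, not individuals.
- That patients were selected. Predictability is an opportunity; no selection is shown.

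Finally, an added sensitivity analysis could sit in an analysis plan that is not shown. Its absence is therefore not the finding. The finding is the stated randomisation rule, and the check is offered as a remedy.

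**Conclusion.** The point holds as a modest design weakness. With fixed blocks of 4 per site and open arms, one third of allocations are certain and 71% guessable at the moment of randomisation. With one intervening patient this becomes 1/12 and 58%. Both sets of figures assume someone who knows or infers the block size and follows every allocation in the list.

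Before April 2022 the tracking would have been within site and cancer type; the share per complete block is the same. Any effect on time to detection is unknown. The illustration in step 5 shows only that moderate steering could matter for a one-sided 5% test. The sample size calculation is not affected.

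**What to change.** 1. If randomisation is still open, have the biostatistician load new site tables with randomly varying block sizes (for example 4, 6 and 8) that are not disclosed to enrolling staff. The gain is mainly in certain allocations (about 2%), since best-guess accuracy falls only to about 68%. Non-disclosure therefore matters as much as variation. Few patients may be affected: at steady accrual the last month is 198/24, or about 8.
2. For patients already randomised, add a Berger-Exner check. Compute each patient's probability of intervention given the earlier allocations in the block (0, 1/3, 1/2, 2/3 or 1). Do this within site, and within site and cancer type for those randomised before the April 2022 amendment. Then relate baseline characteristics, and the primary outcome given arm, to that probability.
3. State predictability of allocation among the limitations.

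Cost: one new REDCap table, slightly larger possible imbalance per site, and one analysis on data already held. The check has limited power at this size, so a null result reassures without proving absence of selection. Label: cheap improvement.

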### Intervention

The intervention of this RCT consists of a complementary model of care that uses ePROs to facilitate remote symptom management [42]. This model is represented in Figure 2. Patients in the intervention arm have access to a weekly PRO-CTCAE questionnaire through an electronic mobile app. Patients receive an email invitation to access the app and an information sheet explaining its interface. Once patients access the app, they are required to complete a questionnaire of predefined symptoms. During the first 3 months of the intervention, active symptoms are reassessed daily. When replying to a questionnaire, patients can add any other item of the full PRO-CTCAE item library, which are automatically added to the following daily or weekly questionnaires as well (see Multimedia Appendix 2). The rapid and sudden onset of IrAE and ICI’s interference with pre-existing conditions and symptoms drove the decision to collect symptom data daily [10,28]. Due to the potential burden this sustained frequency could represent to patients, this was restricted to the first 3 months of the intervention. Patient replies are available in real time to the triage nurses. Two triage nurses at each site are notified via email when patients submit new replies or report severe symptoms, and they contact patients by telephone in the event of new or worsening symptoms. The nurses review patients’ answers every working day from 8 AM to noon. Outside of these hours, usual care procedures apply.

